## Procedure for discontinuation of a clinical trial per subject.

The investigator decides whether the subject can continue the trial and, if not possible, follows the procedure for discontinuation.

- - - 1. The investigator or subinvestigator should promptly explain the discontinuation of the clinical trial to

the subject concerned and the surrogate if any, and take necessary measures such as provision of

appropriate medical care and guidance on health management.

2) Information on subjects collected in accordance with the study protocol before discontinuation of the study will be analyzed in accordance with section 13 of the study protocol.

3)　For subjects who have received an investigational drug, check safety after discontinuation of the investigational drug.

# Adverse event

## Definition of adverse events.

An 'adverse event' is any unwanted or unintended sign (including abnormal laboratory values), symptom or disease that occurs in a subject to whom an investigational drug has been administered, regardless of whether or not it is causally related to the investigational drug. Signs, symptoms or diseases that were present before the investigational drug was administered and that worsen afterwards are also considered adverse events, but signs, symptoms or diseases that were present before consent to participate in the trial and that do not worsen significantly, or physiological changes that are not considered clinically significant in terms of frequency or severity of occurrence, are not considered adverse events.

Among adverse events, those for which a causal relationship with the investigational drug cannot be denied, i.e. those events in "Events with a causal relationship in Table 11.2.3", are referred to as "adverse reactions". An adverse event is said to be an 'unanticipated adverse event' if the adverse event is not described in the investigational new drug summary, or if it is described, but the number, frequency, conditions of occurrence, severity and other trends of occurrence do not match those described. Adverse events that meet the definition in '9.2.5 Severity of adverse events' are also referred to as 'serious adverse events'.

## Assessment of adverse events

The investigator or sub-investigator should enter the following information in the case report form for all adverse events observed during the trial. If more than one adverse event is observed, enter each event separately.

1. Name of adverse event
2. date of appearance
3. Severity (see 9.2.2)
4. Severity (non-serious and serious)
5. Causal relationship with investigational drug
6. treatment
7. Outcome (recovered, mildly recovered, not recovered, recovered but with sequelae, dead, unknown) and date of outcome

### Determination of adverse events

　Abnormal laboratory values or vital signs that are accompanied by clinical symptoms, require interruption or discontinuation of the investigational drug, require medical intervention such as changing concomitant medications, or are judged to be clinically significant findings by the investigator or sub-investigator should be reported as adverse events.

### Severity of adverse events.

The investigator or sub-investigator assesses the severity of the adverse event according to the following criteria.

Mild: usually transient, does not impair the subject's daily life and does not require treatment (normal activities are possible)

Moderate: to the extent that it interferes somewhat with the subject's daily life, causes sufficient discomfort and requires treatment (with discomfort in activities).

Severe: to the extent that the subject's performance of daily activities is significantly impaired and requires treatment (difficulty in performing normal activities).

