### Major adverse events foreseen in this trial

1. Nausea, nausea and vomiting
2. Diarrhoea
3. Feeling that one's skin is itchy
4. Abnormal liver function (increased AST, ALT, ALP)

The frequency of occurrence, calculated from the combined results of clinical trials and post-marketing surveillance up to the time of approval, ranged from 0.1% to less than 5% in all cases.

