## Response to adverse events.

### Dealing with anticipated adverse events.

In the event of an adverse event, the investigators and sub-investigators should provide appropriate first aid, pay attention to ensuring the safety of the subject, and endeavour to resolve and investigate the cause by having the subject undergo diagnosis and treatment by a specialist physician when necessary.

For each anticipated adverse event, take the following actions

1. For nausea, nausea and vomiting, careful follow-up or antiemetics should be administered according to symptoms.
2. For diarrhoea, careful follow-up or intestinal regulators should be administered according to symptoms.
3. Careful follow-up or anti-allergic agents should be administered for itching, depending on the symptoms.
4. If liver function abnormalities (increased AST, ALT, ALP) exceed three times the upper limit of the institutional reference value, the investigator (subcontractor) will inform the study coordinating investigator of the results of a thorough examination of the causal relationship with the investigational drug and discuss the need to discontinue the investigational drug.

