### Safety analysis

1) Analysis of adverse events and adverse events for which a causal relationship cannot be ruled out

　　For each investigational drug group (active drug group and placebo group), the number of adverse events by event (SOC and PT in the latest version of MedDRA) and by severity of the event, the number of occurrences and the percentage of occurrences (number of occurrences/number of evaluable cases) are tabulated. The same tabulation is also carried out for adverse events for which a causal relationship with the investigational drug cannot be ruled out.

2) Analysis of laboratory values

　A time trend diagram should be prepared for each subject over the entire observation period for haematological tests, blood biochemical tests and urinalysis. The number of cases and percentage of occurrence of laboratory abnormalities will be calculated.

3) Serious adverse events.

　　Narrative for each individual event.

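### The adverse event severity scale has no laboratory criterion, so a symptom-free liver enzyme rise cannot be graded above Mild if untreated and fits no grade if treated

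*Protocol*

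**What the plan says.** Protocol section 11.2.1 lists four grounds on which an abnormal laboratory value becomes an adverse event. One is the presence of clinical symptoms. The other three need none: the value may "require interruption or discontinuation of the investigational drug", it may call for medical intervention, or the investigator may judge it clinically significant.

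Section 11.2.2 then gives one three-level scale for all adverse events:

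- The lowest level reads "Mild: usually transient, does not impair the subject's daily life and does not require treatment (normal activities are possible".
- The next level up, called Moderate, is for an event that is present "to the extent that it interferes somewhat with the subject's daily life, causes sufficient discomfort and requires treatment".
- The top level, called Severe, is for an event that is present "to the extent that the subject's performance of daily activities is significantly impaired and requires treatment".

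Section 11.3.1 names four foreseen events. One of them is defined by laboratory values: "Abnormal liver function (increased AST, ALT, ALP". Section 11.4.1(4) contains the protocol's only numeric liver threshold. When the enzymes "exceed three times the upper limit of the institutional reference value", the investigator examines causality and discusses with the coordinating investigator whether the drug needs to be discontinued.

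Section 14.3.2 tabulates adverse events for each arm by MedDRA system organ class and preferred term and "by severity of the event, the number of occurrences and the percentage of occurrences". It also provides time plots of laboratory values for each subject, counts and percentages of laboratory abnormalities, and a narrative for each serious event.

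**The concern.** The reporting rule and the grading rule do not fit together. Section 11.2.1 lets a laboratory value be an adverse event with no symptoms at all. Section 11.2.2 grades that event on a scale whose upper two levels depend on what the subject feels and can do. It contains no laboratory value, no multiple of the upper limit and no criterion for what was done with the study drug.

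Raised liver enzymes may well cause no symptoms, and they are the one laboratory risk that the protocol foresees. An enzyme rise that ended a subject's treatment could appear in the severity table beside trivial events, or be graded differently at each of the five sites because no level fits. With 20 subjects per arm, one or two such events could shape the safety statement on the liver, so the grade given to each of them counts.

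**Working it through.** The protocol states no figure on this point, so there is nothing to reproduce. The check is a reading of the grade definitions, followed by a rough scale.

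**Step 1. Which grade can be met?** Take the section 11.2.2 conditions as written and run through the combinations.

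| Daily-life impairment | Treatment needed | Grade whose conditions are met |
| --- | --- | --- |
| None | No | Mild |
| None | Yes | No grade |
| Some | No | No grade |
| Some | Yes | Moderate, if there is also discomfort |
| Significant | No | No grade |
| Significant | Yes | Severe |

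A symptom-free event lies in the first two rows. Neither leads to Moderate or Severe.

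**Step 2. Apply this to the symptom-free grounds in section 11.2.1.**

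- Drug interrupted or stopped, nothing else done: Mild. If stopping the drug is itself counted as treatment, no grade fits; Moderate and Severe still fail on daily-life impairment.
- Medical intervention given: no grade fits.
- Judged clinically significant and only followed up: Mild.

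The size of the rise enters none of these lines. A value just above three times the upper limit and one many times higher get the same result. The transience wording under Mild makes that grade an awkward fit for a persistent rise, but it opens no path to a higher one.

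**Step 3. Does another rule supply the degree?** The threshold in section 11.4.1(4) leads to a causality examination and a discussion; it assigns no grade. Seriousness (section 11.2.5) is defined independently of severity, so it assigns none either.

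**Step 4. Scale only.** Inputs:

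- 20 active subjects (section 8.2).
- Abnormal liver function in 4 of 222 post-marketing cases, 4/222 = 1.8% (section 3.2.5).
- Raised AST in 2 of 40 and raised ALT in 2 of 40 pre-approval patients, 5.0% each (section 3.2.5). The protocol does not say whether these are the same patients; 5.0% is used as a single rate.
- Lower bound of 0.1% for the foreseen events (section 11.3.1).

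Expected number = 20p. Chance of at least one = 1 − (1 − p)^20.

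| p | Expected | Chance of at least one |
| --- | --- | --- |
| 0.1% | 20 × 0.001 = 0.02 | 1 − 0.999^20 = 0.020 |
| 1.8% (4/222) | 20 × 4/222 = 0.36 | 1 − (1 − 4/222)^20 = 0.305 |
| 5.0% | 20 × 0.05 = 1.0 | 1 − 0.95^20 = 0.642 |

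To whole percentages these are 2%, 30% and 64%.

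**The case against.** The strongest reply is that the harm is shown elsewhere. Section 14.3.2 lists each event under its preferred term whatever its grade, counts laboratory abnormalities separately, plots each subject's values and gives a narrative for serious events. An extreme rise could be classed as serious under section 11.2.5 even with a Mild grade. All of this stands. A reader might infer that liver harm would be hidden in this trial; the protocol does not support that. What is lost is the degree of harm on one axis of one table.

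A second reply is that reporting is largely in order. Section 11.4.1(4) sits among actions for anticipated adverse events, and a value that prompts a causality examination and a discussion of discontinuation would ordinarily count as clinically significant under section 11.2.1. This also stands, so wording on reporting would only clarify.

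A third is that 30% to 64% does not measure the defect. That is correct. The rates cover liver events of any size, in other diseases, and the 5.0% rate lies just outside the range below 5% in section 11.3.1. The share that is symptom-free, above the threshold or led to stopping is not given, so the figures must not be read as the chance of a misleading grade. With so few events, no grading would separate the arms reliably.

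A fourth is that the statistical analysis plan, not available here, could tabulate enzymes by multiples of the upper limit. It could, and that would help. But investigators assign the grade and enter it in the case report form (sections 11.2 and 11.2.2), so an added table would leave the recorded grades, and the severity table built on them, as they are.

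**Conclusion.** The point holds as a defect in a stated rule. Followed literally, section 11.2.2 cannot grade an untreated, symptom-free AST, ALT or ALP rise above Mild, and gives no grade to a treated one, at any multiple of the upper limit. The severity table in section 14.3.2 then cannot show the degree of the only foreseen laboratory risk.

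It does not follow that every symptom-free rise would be recorded as Mild: treated ones fit no level, and investigators may improvise.

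The size is modest. About 0.4 to 1.0 liver events of any kind are expected in the active arm if the section 3.2.5 rates carry over to SCA6 patients, and 0.02 at the 0.1% lower bound. An unknown part of these would meet the problem. The conclusion itself rests on the wording of the scale and not on these rates. It is worth correcting because each such event would weigh heavily in an arm of 20 and the correction is cheap.

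**What to change.** In section 11.2.2, keep the three-level scale for signs and symptoms and add a separate rule for laboratory adverse events. Grade them by multiples of the institutional upper limit, for example with a fixed published laboratory grading table mapped to the three levels. The sponsor should set the cut-offs and reconcile them with the three-times threshold already in section 11.4.1(4). Use these grades in the section 14.3.2 severity table.

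As a clarification, section 11.2.1 could state that AST, ALT or ALP values above that threshold are recorded as adverse events.

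This alters classification and recording only; the management and discontinuation provisions stay as written. The cost is a short amendment and a grading table. No new data are needed, because the enzymes are already measured at screening, on day 0 and at each scheduled visit from week 4 to week 52 (section 8.5). The downside is that a few laboratory events will be graded higher than they are now.

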### Causal relationship between investigational drug and adverse events.

The assessment of a causal relationship between the investigational drug and the adverse event is performed by the investigator or sub-investigator according to Table 11.2.3. If a causal relationship between the investigational drug and the adverse event cannot be ruled out, the assessment is 'causal'.

Table 9.2.3 Assessment of the causal relationship between the investigational drug and the adverse event

| Assessment of causality | causally related  (where a causal link cannot be ruled out). |
| --- | --- |
|  | No causal relationship |

### Predictability of adverse events.

Adverse events that cannot be predicted from the investigational drug summary of the investigational drug in question (including adverse effects that have already been reported to the Minister of Health, Labour and Welfare by the investigator), such as the occurrence of such events, etc. or the trend of occurrence, including the number of occurrences, frequency of occurrences and conditions of occurrence, should be classified as "unpredictable" or "unknown" and predictable as "predictable" or "known". The following should be used.

### Severity of adverse events

Serious adverse events are defined as any of the following, regardless of the severity of the adverse event.

- - 1. death
    2. Threatening to cause death.
    3. Admission to a hospital or clinic for treatment^*^ or extended hospital stay required
    4. disability
    5. Items that may lead to disability.
    6. (i) Those that are serious according to (i) to (v).
    7. Congenital diseases or anomalies in later generations

*In this clinical trial, 'hospitalisation' means staying at a medical institution for one or more nights to receive treatment, and does not include prolonged outpatient treatment such as intravenous infusion or hospitalisation for the purpose of tests. In the case of prolonged treatment in the emergency department, the investigator or sub-investigator will consider the situation and decide whether it should be regarded as a hospitalisation.

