### Follow-up of adverse events that cannot be ruled out as causally related to the investigational drug

Adverse events occurring during the trial period should be followed up as far as possible until recovery occurs or the event is deemed no longer clinically necessary. The method of inpatient or outpatient visits, or in the case of outpatients, the frequency of visits and test items, etc., should be determined by the investigator or sub-investigator, depending on the type and severity of the relevant adverse event. However, if there is a reasonable reason to terminate the investigation in the middle of the study, the investigator or sub-investigator may terminate the follow-up investigation by stating the reason in the original documents such as the medical record.

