## Handling of serious adverse events.

If an adverse event occurs in a subject receiving an investigational drug and the investigator or others consider the event to be serious as per section 11.2.5, the adverse event information should be handled according to the following procedure.

Details on how to respond to the occurrence of a serious adverse event are in accordance with the Procedures for Handling Safety Information.

1) Reporting from the investigator to the head of the site, the clinical trial coordinator and the investigational drug provider

The investigator should report such adverse event information as soon as possible to the head of the investigational medical institution, regardless of causal relationship, as well as to the trial co-ordinator and the investigational drug provider.

2) Notification by the clinical trial coordinator to the investigators at each site

The clinical trial co-ordinator reviews the content of the adverse event report obtained from the investigator and notifies the relevant adverse event information to the investigators at each of the other sites.

3) Discussions between the investigator and the coordinating investigator

The investigator at each site checks the report obtained from the clinical trial co-ordinator, discusses it with the clinical trial co-ordinator as necessary and reports his/her opinion as the clinical trial co-ordinator (including the need for a report to the Minister of Health, Labour and Welfare) to the clinical trial co-ordinator.

4) Report to the Minister of Health, Labour and Welfare

If a report to the Minister of Health, Labour and Welfare is required, the Clinical Trial Co-ordinator should prepare Forms 7 and 8 and an organising sheet and report to the National Institute for Pharmaceuticals and Medical Devices (hereinafter referred to as 'NHI').

5) Reporting to the head of the implementing medical institution

When a report is made to the Minister of Health, Labour and Welfare on a serious adverse event that occurred at another medical institution, the investigator should report the contents of Forms 7 and 8, obtained from the clinical trial coordinator, to the head of the implementing medical institution as soon as possible.

6) Action to be taken when additional information is available.

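### The seriousness definition in Protocol 11.2.5 excludes hospital stays for tests without limiting this to planned or unrelated tests, so an overnight stay solely to investigate an adverse event is not serious under the hospitalisation item

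*Protocol*

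**What the plan says.** Protocol 11.2.5 lists seven seriousness items. Item 3 reads "Admission to a hospital or clinic for treatment^*^ or extended hospital stay required". The footnote to it gives a trial-specific meaning: hospitalisation "means staying at a medical institution for one or more nights to receive treatment", and it "does not include prolonged outpatient treatment such as intravenous infusion or hospitalisation for the purpose of tests". One borderline case is left to judgement: "In the case of prolonged treatment in the emergency department, the investigator or sub-investigator will consider the situation and decide" whether it is to be regarded as a hospitalisation. No such discretion is given for admissions for tests.

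Protocol 11.5 starts the serious-event procedure when the investigator or others "consider the event to be serious as per section 11.2.5". Protocol 14.3.2 plans a narrative for each serious event, and counts and percentages for adverse events in general.

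**The concern.** Leaving out admissions for tests is sensible for a planned check-up, which is not a harm. The footnote has no word that confines it to that case. By its plain wording it also covers a stay that an adverse event has caused and whose purpose is to find out what is wrong.

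The serious label decides what happens next. Under 11.5 it brings a report, whatever the causality, to the head of the site, the coordinator and the drug provider. It also brings a notice to the other sites and a view on whether the ministry must be told. Under 14.3.2 it brings a narrative. The protocol states that L-arginine has not been tried before in this disease (3.2.5), and safety is part of the objective (section 4). Five sites take part, so the same stay could be classified differently according to whether a site calls it tests or treatment.

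**Working it through.** No arithmetic applies, and the protocol gives no figure on this point. The check takes one type of event through the text: an adverse event leads to at least one night in hospital, the purpose is examination only, and no treatment is given.

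1. **Item 3, first part (admission).** The admission must be for treatment, and the footnote repeats that condition. The stay fails it. The footnote then excludes stays for tests expressly, so the stay fails twice.
2. **Item 3, second part (extended stay).** This can apply only if the subject was already in hospital. The text does not say whether the tests exclusion also applies to a prolongation. A new admission does not reach this part.
3. **Items 1, 2, 4, 5 and 7** (death, threat to life, disability, possible disability, congenital anomaly). These depend on the event and not on the stay. If any of them is met, the event is serious and the exclusion does no harm.
4. **Item 6.** This is the residual category, garbled in the text (it reads "Those that are serious according to (i) to (v"). It seems to mean events comparable in seriousness to the first five items. An investigator could use it, but it does not mention diagnostic stays.
5. **Other adverse event text.** Sections 11.1, 11.2, 11.2.1, 11.2.2, 11.4, 11.5 and 14.3.2 contain nothing that narrows the exclusion.

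If steps 1 to 4 all come out negative, the consequences are:

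| Provision | What happens to the event |
| --- | --- |
| 11.2 and 11.4.3, case report entry | Kept: recorded as a non-serious adverse event |
| 14.3.2(1), tabulation by event and severity | Kept |
| 11.4.1(4), AST, ALT or ALP above three times the upper limit | Kept: the coordinating investigator is informed whether or not the event is serious |
| 11.5, serious-event reporting | Lost |
| 14.3.2(3), individual narrative | Lost |

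The protocol does foresee that adverse events are investigated and that some lead to hospital. Section 3.2.6 warns that unforeseen events may lead to admission. Section 11.4.1 asks for the cause to be sought, with specialist diagnosis where needed. Section 11.4.2 leaves to the investigator "The method of inpatient or outpatient visits, or in the case of outpatients, the frequency of visits and test items, etc". None of these sections describes an admission for tests alone. They make such a stay plausible and do not show that one is expected.

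**The case against.** The strongest reply is that the affected set is small and the event data survive. An event is lost to serious-event handling only if the stay is overnight, is for tests alone, includes no treatment, is not a required extension of an existing stay, meets no other item, and is not brought in under item 6. The footnote defines one term for one item and does not declare the event non-serious. Residual criteria always work by individual judgement, and 11.5 itself rests on what the investigator or others consider serious. In addition, 11.5 leaves details to a separate safety information procedure that is not at hand and may already settle the matter. All of this stands, and it limits the size of the point. It does not remove it, because 11.5 sends the seriousness decision back to 11.2.5, where the only explicit statement about stays for tests is an unlimited exclusion.

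A reader might infer more than the protocol supports:

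- **That any hospital work-up of a suspected drug harm escapes serious-event reporting.** It does not. Treatment during the stay, or any other item, is enough to qualify.
- **That the protocol plans such stays.** The phrase "the results of a thorough examination of the causal relationship with the investigational drug" in 11.4.1(4) concerns an assessment of causality and says nothing about admission. Section 11.4.2 leaves the setting of follow-up open and does not mention admission for tests.
- **That a liver signal could pass unnoticed.** Above the threshold in 11.4.1(4) the coordinating investigator is told in any case. The head of the site, the drug provider and the other sites are not named there.
- **That the serious event rate is biased by a known amount.** With 20 subjects per arm, one subject is 1/20 = 5 percentage points, but that holds for any event in any arm of 20. It says nothing about how often this gap would matter. For serious events, 14.3.2 specifies narratives and no comparison between arms.

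**Conclusion.** The point holds in a narrow form. Following 11.2.5 as written, an overnight stay solely to investigate an adverse event does not meet the hospitalisation item. If no other item applies and item 6 is not invoked, the event goes without serious-event reporting and without a narrative, although it stays in the adverse event record and tables.

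The frequency of such stays cannot be derived from the protocol, and no figure is put on it. The conclusion rests on two assumptions: that sites apply the footnote literally, and that the separate safety information procedure does not already limit the exclusion. The protocol does not contradict itself here. A stated rule is wider than its evident purpose, and that is cheap to correct.

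**What to change.** In the footnote to 11.2.5:

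- limit the exclusion to admissions for tests that were planned before the event or are unrelated to any adverse event;
- state that an overnight stay to examine or observe an adverse event counts as hospitalisation under item 3.

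Align the separate safety information procedure with this wording if it does not already say so.

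The cost is about one sentence in the protocol, possibly one in the procedure, and a few more serious adverse event reports. Planned check-ups remain excluded.
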